## Abstract

**Background:**

In pressure support ventilation (PSV), a non-variable level of pressure support is delivered by the ventilator when triggered by the patient. In contrast, variable PSV delivers a level of pressure support that varies in a random fashion, introducing more physiological variability to the respiratory pattern. Experimental studies show that variable PSV improves gas exchange, reduces lung inflammation and the mean pressure support, compared to non-variable PSV. Thus, it can theoretically shorten weaning from the mechanical ventilator.

**Methods/design:**

The ViPS (variable pressure support) trial is an international investigator-initiated multicenter randomized controlled open trial comparing variable vs. non-variable PSV. Adult patients on controlled mechanical ventilation for more than 24 hours who are ready to be weaned are eligible for the study. The randomization sequence is blocked per center and performed using a web-based platform. Patients are randomly assigned to one of the two groups: variable PSV or non-variable PSV. In non-variable PSV, breath-by-breath pressure support is kept constant and targeted to achieve a tidal volume of 6 to 8 ml/kg. In variable PSV, the mean pressure support level over a specific time period is targeted at the same mean tidal volume as non-variable PSV, but individual levels vary randomly breath-by-breath. The primary endpoint of the trial is the time to successful weaning, defined as the time from randomization to successful extubation.

**Discussion:**

ViPS is the first randomized controlled trial investigating whether variable, compared to non-variable PSV, shortens the duration of weaning from mechanical ventilation in a mixed population of critically ill patients. This trial aims to determine the role of variable PSV in the intensive care unit.

**Trial registration:**

clinicaltrials.gov NCT01769053

## Background

Around 40% of the total duration of mechanical ventilation is spent in the weaning process [1-3]. Both prolonged mechanical ventilation, as well as premature extubation, are associated with severe complications. For example, the risk of developing pneumonia increases with the duration of mechanical ventilation [4,5] and with re-intubation [6]. More importantly, failed extubation is associated with an increase in the risk of death [7]. Therefore, delivery of mechanical ventilatory support for the shortest possible time is the state of the art in intensive care medicine [8].

Pressure support ventilation (PSV) is the commonest form of spontaneous assisted mechanical ventilation worldwide [3]. During weaning with PSV, the pressure support applied by the ventilator is reduced in a stepwise manner until a minimal level of support is achieved. During classical (non-variable) pressure support, each spontaneous breath is supported by a constant set level of pressure at the airways. Thus, breath-by-breath variability of tidal volume (*V*_
*T*
_) and respiratory rate (RR) is mainly determined by the patient’s respiratory drive. A low respiratory drive, due to underlying disease and/or deep sedation, may result in a respiratory pattern with minimal or no variability despite the spontaneous breathing.

Decreased variability in *V*_
*T*
_ and RR is associated with delayed weaning from mechanical ventilation in a mixed intensive care unit (ICU) population [9]. In patients recovering from sepsis, increased variability of *V*_
*T*
_ and RR is a reliable predictor of weaning success [10]. However, those studies were conducted retrospectively and, to our knowledge, no study has tested whether weaning from mechanical ventilation can be made shorter by increasing the variability of the tidal volumes using variable levels of pressure support. A possible reason for the lack of such a study might be because assisted modes of mechanical ventilation resulting in more variable respiratory patterns (for example, proportional assist ventilation and neurally adjusted ventilatory assist) depend on the intrinsic variability of the respiratory system. Another likely explanation is that a desired mean *V*_
*T*
_ is difficult to guarantee in closed-loop systems that sense the inspiratory effort, making comparisons of variable with non-variable assisted mechanical ventilation at a predefined mean *V*_
*T*
_ difficult.

In 2008, a new ventilation strategy termed variable (or noisy) PSV was introduced. Variable PSV is able to increase the variability of the respiratory pattern independent of the inspiratory effort [11]. Thereby, matching of *V*_
*T*
_ between variable and non-variable PSV can be easily accomplished. Preliminary observations suggest that variable PSV has the potential to reduce patient-ventilator asynchrony, but it is uncertain whether this is associated with a shorter duration of weaning from mechanical ventilation.

Since variable PSV can reduce the mean pressure support [12], it may lead to a faster reduction of pressure support and, therefore, a shorter weaning period than non-variable PSV. We describe the design of the first randomized controlled trial of variable PSV for weaning from mechanical ventilation in a mixed intensive care unit population.

## Methods/design

### Objectives and design

The ViPS trial is an international investigator-initiated multicenter randomized controlled open trial comparing variable vs. non-variable pressure support ventilation in patients receiving mechanical ventilation for more than 24 hours who are able to be weaned. The Ethics Committee of the Dresden University of Technology has approved the protocol of the trial. The ViPS trial is conducted in accordance with the declaration of Helsinki and was registered on 18 December 2012 as a clinical trial [13] with trial identification number NCT01769053.

The objective of the study is to test whether variable compared to non-variable pressure support ventilation effects the duration of weaning from mechanical ventilation. The hypothesis of the ViPS trial is that variable pressure support ventilation will shorten the duration of weaning from mechanical ventilation compared to non-variable pressure support ventilation by two days. Figure 1 shows the consolidated standards of reporting trials (CONSORT) diagram of the ViPS trial.

**Figure 1 F1:**
[figure not shown]
**CONSORT diagram of the trial.***P*_supp_ is the level of pressure support.

### Patient screening

Consecutive intensive care unit patients who are on controlled mechanical ventilation for more than 24 hours are eligible for the trial. Local investigators screen patients admitted to ICU on a daily basis. All patients, their legal representative or an independent physician not involved with the study, depending on local regulations, are asked for signed informed consent, as required by the local ethics committee in accordance with the declaration of Helsinki.

### Inclusion and exclusion criteria

The inclusion criteria are the following: age ≥18 years; duration of controlled mechanical ventilation ≥24 h; temperature ≤39°C; hemoglobin ≥6 g/dl; ratio of arterial partial pressure of oxygen to inspiratory oxygen fraction PaO_2_/FiO_2_ ≥ 150 mmHg with positive end-expiratory pressure (PEEP) ≤16 cmH_2_O; ability of the patient to breathe spontaneously; availability of a mechanical ventilator with the capability for variable PSV and informed consent according to local regulations.

The following exclusion criteria have been defined: the patient has participated in another interventional trial within the last four weeks before enrolment in the ViPS trial; peripheral neurological disease associated with impairment of the respiratory pump; muscular disease associated with impairment of the respiratory pump; unstable thorax with paradoxical chest wall movement; planned surgery under general anesthesia within 72 hours; difficult airway or intubation; existing tracheotomy at ICU admission; expected survival <72 hours; home mechanical ventilation or on chronic oxygen therapy and suspected or confirmed pregnancy of the patient.

### Pre-inclusion test

Upon giving informed consent and after confirming agreement with the inclusion and exclusion criteria, a patient is monitored for spontaneous breathing activity. The transition from controlled to assisted ventilation is observed by a so-called pre-inclusion Test. After switching controlled mechanical ventilation to pressure support mode, every patient has to fulfill specific criteria for a period of one hour. This phase is to ensure that patients in both treatment groups show uniform stable spontaneous breathing activity. The time at which spontaneous breathing activity occurs will be recorded. This initial test can be interrupted and controlled mechanical ventilation resumed if the patient shows signs of hemodynamic or respiratory distress during the pre-inclusion test.

The pre-inclusion test is considered successfully passed if: temperature ≤39°C; PaO_2_/FiO2 ≥ 150 mmHg with PEEP ≤16 cmH_2_O; pH ≥ 7.30; respiratory rate ≤40/min; heart rate 40 to 130/min; systolic blood pressure >80 or <160 mmHg; a dose of noradrenaline or adrenaline <0.1 mcg/kg/min, dopamine or dobutamine <2 mcg/kg/min; no hemodynamically relevant acute cardiac arrhythmias occur.

If the patient fails the test criteria, the test will be repeated after patient recovery, at the treating physician’s discretion. Randomization only occurs after the patient passes the pre-inclusion test.

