### Extubation criteria

As the ventilator settings are reduced in a stepwise manner to reach the extubation criteria, the patient’s condition is continuously monitored. As soon as the patient fulfills the following extubation criteria for a time period of at least 30 minutes, extubation is possible:

Richmond agitation and sedation scale (RASS) ≥ −3; behavioral pain scale (BPS) ≤5 or visual analogue scale (VAS) for pain ≤3; raising hands or legs against gravity; temperature ≥36°C and ≤39°C; ability to cough to clear secretions after deflating cuff; respiratory rate 8 to 30/min; PaO_2_/FiO_2_ ≥ 200 mmHg (≥150 mmHg in patients with chronic obstructive pulmonary disease); pressure support ≤8 cmH_2_O; PEEP ≤8 cmH_2_O; systolic blood pressure 80 to 160 mmHg; heart rate 40 to 130/min and no hemodynamically relevant arrhythmia.

If extubation has occurred and the patient needs to be re-intubated within 72 hours, the extubation is defined as not successful and the assigned study mechanical ventilation mode will be reinstituted as soon as possible. Successful extubation is defined as extubation lasting 72 hours.

Non-invasive ventilation (NIV) after extubation is allowed after extubation according to local practice. However, if a PEEP level >8 cmH_2_O, or pressure support >8 cmH_2_O is required for NIV, the extubation is considered not successful.

If the patient has to receive tracheotomy during the study period, assisted mechanical ventilation will be resumed as soon as possible via the tracheal cannula according to the assigned therapy group. In tracheotomized patients successful extubation is defined as patient separation from the ventilator without reconnection for <72 h after separation. If continuous positive airway pressure (CPAP) therapy via the tracheal cannula with PEEP >8 cmH_2_O or pressure support >8 cmH_2_O is required, the separation from the mechanical ventilator is considered not successful. The study-related intervention is finished on successful extubation. Patients will be observed until ICU and hospital discharge and contacted during the follow-up period.

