### Statistical considerations

#### Sample size calculation

The sample size calculation (GPower software version 3.1.3, University of Düsseldorf, Germany) was based on the Wilcoxon–Mann–Whitney test (two groups, two tailed). The calculation was based on the expectation that the primary endpoint variable (time from randomization to successful extubation) would show a difference of 2 days between the two treatment groups. Based on the study by Lellouche *et al*. [14] the standard deviation (SD) was estimated as 5 days for both groups, yielding an effect size (*d*) of 0.4. Accordingly, 104 patients per group would allow the detection of differences between the groups with a power of 80% and a type one error rate of 5%. Assuming that 10 dropouts per group may occur, 228 patients in total are necessary.

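### The systolic blood pressure item of the pre-inclusion test is joined by an or, so every value passes and no pressure limit applies before randomisation

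*Protocol article*

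**What the plan says.** The section Pre-inclusion test describes a one-hour period on pressure support during which the patient must meet a list of criteria. Its stated purpose: "This phase is to ensure that patients in both treatment groups show uniform stable spontaneous breathing activity". It is the gate to allocation: "Randomization only occurs after the patient passes the pre-inclusion test".

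The list has eight items: temperature, oxygenation ratio with a PEEP ceiling, pH, respiratory rate, heart rate, systolic pressure, catecholamine dose, and absence of relevant arrhythmia. The systolic item reads "systolic blood pressure >80 or <160 mmHg". The heart rate item just before it is a closed range, "heart rate 40 to 130/min".

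Three other places bear on the point:

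- The section Inclusion and exclusion criteria names no blood pressure limit.
- The Pre-inclusion test section also has a stopping clause: "This initial test can be interrupted and controlled mechanical ventilation resumed if the patient shows signs of hemodynamic or respiratory distress". It gives no pressure value.
- The section Extubation criteria, which governs a later stage, gives the same variable as "systolic blood pressure 80 to 160 mmHg".

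**The concern.** A lower and an upper bound on one variable limit it only if both must hold. Here either one is enough. Because the lower bound (80) lies below the upper bound (160), the two half-lines overlap and together cover every possible pressure. The item is always satisfied.

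This is the only numeric blood pressure threshold stated ahead of randomisation. Taken literally, a hypotensive or severely hypertensive patient meets it, and randomising such a patient would not count as an eligibility deviation on this item. The remaining protection is the other seven items, none of which contains a pressure value, and a stopping clause that is permissive and has no threshold. For example, the catecholamine item caps dose only, so a patient at 60 mmHg on no vasopressor meets both that item and the pressure item.

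What is at stake is who may be randomised and how safely. The treatment comparison itself is not at stake.

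**Working it through.** **Inputs.** The systolic item and the heart rate item come from the section Pre-inclusion test; the comparison range comes from the section Extubation criteria.

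**Step 1: the rule as written.** It passes if SBP > 80 or SBP < 160.

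- If SBP ≤ 80, then SBP < 160 is true, so the patient passes.
- If 80 < SBP < 160, both parts are true, so the patient passes.
- If SBP ≥ 160, then SBP > 80 is true, so the patient passes.

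No value is left over. Checking every whole number from 0 to 300 mmHg (301 values) gives 0 failures.

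**Step 2: the two possible repairs.**

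- Strict: SBP > 80 and SBP < 160. It fails 0–80 (81 values) and 160–300 (141 values), so 81 + 141 = 222 of 301.
- Inclusive: 80 ≤ SBP ≤ 160. It fails 0–79 (80 values) and 161–300 (140 values), so 80 + 140 = 220 of 301.

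The two repairs differ only at exactly 80 and exactly 160 mmHg.

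**Step 3: illustration.** These five pressures were chosen to show the logic, and two of them sit on the boundaries on purpose. The counts say nothing about how often such pressures occur in patients.

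| SBP (mmHg) | As written (or) | 80 to 160 inclusive | > 80 and < 160 |
|---|---|---|---|
| 60 | pass | fail | fail |
| 80 | pass | pass | fail |
| 120 | pass | pass | pass |
| 160 | pass | pass | fail |
| 200 | pass | fail | fail |
| Passing | 5 of 5 | 3 of 5 | 1 of 5 |

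**Step 4: extent within the test.** Eight items are listed; one is void as written, and 8 − 1 = 7 still operate.

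**Step 5: the sample size does not depend on this item.** The calculation uses a difference of 2 days and an SD of 5 days, "yielding an effect size (*d*) of 0.4", with 80% power and a two-sided 5% error rate. The normal-approximation formula for two means gives 99 per group. Dividing by the efficiency of the Wilcoxon–Mann–Whitney test under a normal distribution, 3/π = 0.955, gives 99 / 0.955 = 103.7, so 104 per group, as stated. Then 2 × (104 + 10) = 228, also as stated. No blood pressure limit enters these figures.

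**The case against.** The strongest reply is that this is a slip of one conjunction whose meaning nobody would mistake. Both numbers are present, the neighbouring heart rate item is a range, and the Extubation criteria print the systolic range outright. Sites would most likely read 80 to 160 mmHg. That is fair, and it is why the point is a correction and not a fault in the trial's design. It does not make the text right. A pass criterion in an international open trial should not need repair by each site, and inferring the intent does not settle whether exactly 80 or 160 mmHg passes.

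A second reply is that the list uses the same conjunction loosely in the catecholamine item, so it should be read as informal prose. The cases differ. There the word joins drug names and reads naturally as a cap on each drug; here it joins two inequalities on the same variable.

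A third reply is that a patient at 60 mmHg would be expected to show haemodynamic distress and be taken off the test. That is plausible, and the clause is a real protection, but it is discretionary and has no threshold. It is also less obviously triggered by a high pressure.

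Finally, this is an article condensing a fuller protocol, and the wording issued to sites is not visible. That limits the conclusion to the published text but does not correct it.

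**Conclusion.** The concern holds. As written, the systolic item is satisfied by every value, so 1 of the 8 criteria sets no limit, and the article contains no other numeric blood pressure threshold before randomisation.

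This rests on reading the current text literally and on the absence of any blood pressure limit in the inclusion and exclusion criteria. A bounded range was almost certainly intended. The Extubation criteria are evidence of that intent; they apply at a different stage and do not contradict the test.

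The consequence is limited to eligibility and safety wording. The test is applied before 1:1 randomisation, so the error does not bias the comparison between the arms, and the planned 104 per group and 228 in total stand. The number of patients who might be randomised outside the intended range cannot be estimated, because the document gives no distribution of systolic pressure. The item should be corrected because it is an operative threshold for entering the trial.

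**What to change.** In the section Pre-inclusion test, rewrite the systolic item as a bounded range, in one of two forms:

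- greater than 80 and less than 160 mmHg, which keeps the strict signs now printed; or
- 80 to 160 mmHg, which matches the Extubation criteria and the style of the heart rate item.

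The clinical leads should choose between them by stating whether the endpoints 80 and 160 pass, since that is the only difference. It is also sensible to confirm that the protocol issued to sites and the case report form checks carry the same bounded rule.

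The cost is a one-word protocol correction, with no effect on sample size, power or analysis.

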### Randomization

Patients will be randomized using a web-based secure-sockets-layer (SSL) encrypted platform with a randomization sequence blocked per center to yield approximately equal group sizes (block randomization, 1:1 ratio, mixed block sizes maximum block size eight). Patients will be randomly assigned to one of the two groups: variable pressure support ventilation or non-variable pressure support ventilation. The assigned ventilation mode has to be applied immediately after randomization.

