#### Statistical analysis

The descriptive analysis will include the mean and standard deviation for normally distributed variables. Variables that are not normally distributed will be expressed by their medians and interquartile ranges. Categorical variables will be expressed as *n* (%). Differences in the primary endpoint variable, time from randomization to successful extubation between the two treatment groups, will be analyzed by a Wilcoxon–Mann–Whitney test.

To decide on the proper comparison method for the exploratory analysis of the secondary endpoints, we will test whether the variables are normally distributed. Student’s *t*-test will be used to test groups of independent continuous normally distributed variables. The Mann–Whitney *U* test will be used for continuous variables that are not normally distributed. Categorical variables will be compared with the chi-square test or Fisher’s exact test. Paired data will be analyzed using Student’s *t*-test for continuous normally distributed variables, the Wilcoxon test for continuous variables that are not normally distributed and the McNemar or Bowker test, as appropriate, for categorical variables.

Kaplan–Meier survival curves will be computed to evaluate differences in overall survival. Survival curves will be compared by a log-rank test and multivariable analysis will be accomplished by the Cox regression model.

If any patients are lost to follow-up or withdraw consent for the trial, the reasons will be reported. The intention-to-treat (ITT) analysis and per protocol (PP) analysis will be conducted to test whether the result of this trial is reliable. Missing data will be handled by means of the last-observation-carried-forward method. For the intention-to-treat analysis, data will be processed for all trial patients in the groups to which they were randomized, regardless of whether they received or adhered to the allocated intervention.

It is assumed that the majority of patients in the two triage arms will receive the appropriate study intervention. The per protocol analysis will be performed as a secondary analysis if there are sufficient patients in the triage arms who do not receive study therapy or are lost to outcome assessment. Data from participants who do not violate the treatment protocols will be included in the per-protocol analysis.

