The ViPS trial will broaden our knowledge of the impact of variable PSV on important clinical outcome variables in a mixed ICU population. The inclusion and exclusion criteria have been carefully designed to include a large number of patients, regardless of their co-morbidities, while taking safety issues into account. Thereby, the use of variable PSV, which has been evaluated only for hypoxemic lung failure, will be expanded to other patient groups. The protocol described here represents a consensus among centers and investigators with considerable experience in weaning patients from mechanical ventilation. The interventions are an agreement between several weaning strategies conducted in the participating centers, while the variable PSV settings have been carefully derived from experimental knowledge combined with clinical experience. Therefore, compliance of the participating centers to the protocol is likely.

The ViPS trial protocol has limitations that must be addressed. First, the entry criteria allow for patients with large differences in weaning duration, ranging from hours to days. These differences have been considered in the sample size calculation. Second, patients who fail to wean may be transferred to weaning centers, resulting in them being lost to follow-up and, consequently, causing a reduction in study power. Nevertheless, the dropout rates considered in the sample size calculation represent a worst case scenario for the participating centers. Third, the protocol cannot be conducted in a blinded fashion, which can favor bias. To minimize this effect, we defined a tight protocol where intervention steps mandate handling until the primary endpoint is achieved. Fourth, even though the protocol interventions represent a consensus among centers, local differences in weaning experience and standards may still affect the results of this trial. Fifth, the use of non-invasive ventilation following extubation could introduce bias in terms of a reduction of weaning time, but this effect should not affect the comparative performance of variable PSV, since it is also allowed in the control group.

In conclusion, ViPS is the first randomized controlled trial that compares variable with non-variable PSV with respect to the duration of weaning from mechanical ventilation in a mixed ICU population. This trial may also clarify how and why variable PSV improves lung functional variables, and reduces the respiratory drive.

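### Allocation is blocked within centre but the primary Wilcoxon–Mann–Whitney test ignores centre, so it is conservative if weaning time differs between centres

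*Protocol article*

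**What the plan says.** - **Allocation** (Protocol article, Randomization): a "randomization sequence blocked per center to yield approximately equal group sizes", in a 1:1 ratio with blocks of varying size up to eight. The arms are therefore close to balanced inside every centre.
- **Primary analysis** (Statistical analysis): "time from randomization to successful extubation between the two treatment groups, will be analyzed by a Wilcoxon–Mann–Whitney test". No stratum or covariate is attached.
- **Sample size** (Sample size calculation): the calculation "was based on the Wilcoxon–Mann–Whitney test (two groups, two tailed"). The endpoint "would show a difference of 2 days between the two treatment groups", and "the standard deviation (SD) was estimated as 5 days for both groups, yielding an effect size (*d*) of 0.4". This leads to 104 per group for 80% power at a 5% type I error rate, and 228 in total with ten dropouts per group.
- **Centre differences** (Discussion, fourth limitation): "local differences in weaning experience and standards may still affect the results of this trial". No analytic response follows.

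Centre appears in none of the analyses that the article describes.

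**The concern.** The plain rank-sum test takes its null variance from all ways of splitting the pooled patients into two arms. Blocking per centre rules out most splits that are lopsided by centre. If weaning time differs between centres, those excluded splits are the ones that would have moved the rank sum most. The variance that the test assumes is then larger than the variance that the design produces, and the p-value is too large on average.

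Such differences are plausible on the document's own account. Non-invasive ventilation after extubation follows local practice (Extubation criteria). The interval between meeting the criteria and being extubated depends on logistics (Intervention period data), and the primary endpoint runs to the extubation itself.

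At stake is some precision that the design has already created, and agreement between the primary p-value and the way patients were allocated. The validity of a positive result is not at stake.

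**Working it through.** **1. The plan's own figure.** Inputs from Sample size calculation: difference 2 days, SD 5 days, d = 2/5 = 0.4, two-sided 5%, power 80%.

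- Two-sample normal approximation: n = 2(1.96 + 0.8416)² × 5²/2² = 98.1, so 99 per group.
- Divide by the relative efficiency of the Wilcoxon test for normal data, 3/π: 99 × π/3 = 103.7, so 104 per group.
- Noncentral-t power with n scaled by 3/π: 0.801 at n = 104.
- Total: 2 × (104 + 10) = 228.

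The stated size reproduces exactly.

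**2. Expected direction and size.** Let ρ be the share of outcome variance between centres. With perfect balance inside centres, the true variance of the comparison is roughly (1 − ρ) times the variance the plain test assumes. The true size is then about 2Φ(−1.96/√(1 − ρ)):

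- ρ = 0.05: 2Φ(−2.011) = 4.4%
- ρ = 0.10: 2Φ(−2.066) = 3.9%
- ρ = 0.20: 2Φ(−2.191) = 2.8%

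This is an approximate limit. Incomplete last blocks and a finite number of centres bring the size back towards 5%.

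**3. Simulation.** The document gives neither the number of centres nor ρ, so both are assumed. Settings: 208 patients (the 104 per group on which power is based), 5, 10 or 20 equal centres, permuted blocks of 2 to 8 within centre, normal outcome with total SD held fixed, d = 0 or 0.4, and 12,000 trials per setting. Monte Carlo standard error is about 0.2 points for size, √(0.05 × 0.95/12,000), and 0.4 points for power, √(0.8 × 0.2/12,000). Ranges run over the three numbers of centres.

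| Share between centres | Size, plain | Size, stratified | Power, plain | Power, stratified |
|---|---|---|---|---|
| 0 | 4.8–5.1% | 4.7–5.0% | 79–80% | 76–79% |
| 0.05 | 4.4–4.7% | 4.8–5.1% | 80–81% | 78–81% |
| 0.10 | 4.0–4.5% | 5.0–5.3% | 81–82% | 80–83% |
| 0.20 | 3.1–3.4% | 4.8–5.2% | 82–84% | 85–87% |

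**4. Power difference (stratified minus plain) by number of centres, in points.**

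| Share | 5 centres | 10 centres | 20 centres |
|---|---|---|---|
| 0 | 79.3 − 80.1 = −0.8 | 77.8 − 79.5 = −1.7 | 76.3 − 80.2 = −3.9 |
| 0.05 | 80.7 − 80.8 = −0.1 | 80.3 − 80.7 = −0.4 | 77.9 − 80.2 = −2.3 |
| 0.10 | 82.7 − 80.9 = +1.8 | 82.9 − 82.1 = +0.8 | 80.4 − 81.3 = −0.9 |
| 0.20 | 87.3 − 83.7 = +3.6 | 86.8 − 83.1 = +3.7 | 84.8 − 81.9 = +2.9 |

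**5. Unequal centres.** A smaller simulation used 228 patients analysed, ten unequal centres and 3,000 trials per setting. The plain test had a size of 4.0% at a 10% share and 3.4% at 20%, against 5.0% and 5.2% for the stratified test. This agrees with step 3. Its power figures start higher (83.9% for the plain test at share 0) because all 228 patients are analysed. They carry a standard error of up to about 0.7 points, too coarse to separate the tests at small shares.

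**The case against.** The strongest reply is that nothing breaks. The error is on the safe side, and the plain test holds its planned power: 79–80% with no centre effect, rising to 82–84% at a 20% share. The power gain from stratifying is clear only at the largest share tried, and with 20 small centres stratifying loses power even at a 5% share. The article also gives the purpose of blocking as group sizes, not control of a prognostic factor, and it says only that local differences may matter. All of this stands, and it limits the weight of the point.

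A second reply is that centre stratification belongs in an analysis plan that is not shown. This is less persuasive. The article names the primary test and sizes the trial on it, both times as a two-group comparison. A plan that stratified would be changing the stated primary analysis.

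A reader might infer more than the text supports:

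- **That the variance is wrong whatever happens.** It is wrong only if centres differ, and the document does not say that they do.
- **That a significant primary result would be unsafe, or the trial too small.** The size stays at or below about 5%, and 104 per group is reproduced.
- **That stratifying would dispose of the limitation in the Discussion.** It removes differences in level between centres. It does not remove differences in how the intervention is delivered or in its effect.
- **That a time-to-event model for weaning time also needs stratifying.** The Statistical analysis section names the log-rank test and Cox regression in its paragraph on overall survival, not for the primary endpoint.

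**Conclusion.** The point holds conditionally and is modest in weight. The primary test ignores the factor within which patients are randomised. If weaning time differs between centres, its true type I error falls below the nominal 5%: about 4.0–4.5% at a 10% between-centre share and 3.1–3.4% at 20%. These sizes rest on an assumed number of centres (5 to 20), assumed variance shares and a normal outcome. The direction does not depend on the exact values. Matching the test to the allocation is still worth doing, because it needs no patients and answers in part a limitation that the protocol itself raises.

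**What to change.** In Statistical analysis, name the primary test as the Wilcoxon–Mann–Whitney test stratified by centre (van Elteren). Add a rule for pooling small centres, fixed before any outcome data are compared by arm. The trial is open, so the rule cannot be tied to unblinding.

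The change is a line of wording plus the pooling rule. The sample size, the rank-based approach and the conduct of the trial stay as they are. The price is about 2 points of power if centres differ little, or up to 2–4 points with many small unpooled centres. The pooling rule is therefore a necessary part of the change. In return, the size is held at about 5%, with about 3–4 points more power if centres account for a fifth of the variance.
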